### **8.2 INFORMED ASSENT FOR ADULT PREGNANT WOMEN OVER 18 YEARS OF AGE**

Because we recruit women at or over 18 years old, we do not need to perform assent in this study.

### 8.3 WITHDRAWAL OF CONSENT

Even after agreeing to participate in the trial, if the patient wishes, consent can be withdrawn at any time until just before fixing the data of the analyzed population. When withdrawing consent, CI or SI consults with the patient, confirms the reason for the withdrawal of consent, and explains the observation necessary after the consent withdrawal. Thereafter, the consent withdrawal procedure should involve the consent withdrawal document as much as possible. After withdrawal of consent, participation in the study should be discontinued. In order to ensure the safety of the patient after discontinuing participation in the trial, we should endeavor to conduct later observation, such as confirming the physical condition change of the subject, to the extent possible.

## 9 ADVERSE EVENTS AND “DISEASE, ETC.”

Details shall be described in the "Procedures for handling cases of “disease, etc.”.

### 9.1 DEFINITION

#### 9.1.1 DEFINITION OF ADVERSE EVENTS

Adverse events in this study are defined as clinically problematic events among all unfavorable symptoms, signs, illnesses, and laboratory abnormalities that occur in subjects (mother, fetus) from the start of protocol treatment to the termination of pregnancy (or when study participation has discontinued). It does not matter if it has a causal relationship with protocol treatment. In infants, they are defined as clinically problematic events among all unfavorable symptoms, signs, illnesses, or abnormal laboratory abnormalities that occur between postpartum and the end of observation. However, IVH, PVL, RDS, meconium aspiration syndrome (MAS), TTN, PPHN, sepsis, NEC, which are defined as neonatal complications in this trial, localized intestinal perforation, and symptomatic PDA are not reported as adverse events in infants; but they are reported as serious adverse events if they fall under the definition of serious adverse events.

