Thus, although both ABPC/STB + EM and ABPC/STB + AZM are expected to be more effective against BPD than conventional methods, no trials have ever been conducted for BPD using these methods, and therefore no data exist on how good the treatment outcome can be expected. Therefore, we planned a parallel-group study comparing ABPC/STB + EM and ABPC/STB + AZM, rather than a single-arm study using ABPC/STB + AZM, and a phase II study to investigate the safety of ABPC/STB, EM, and AZM. The study was designed to compare the safety of ABPC/STB, EM, and AZM. The data on BPD incidence in both groups obtained in this study will provide essential information for calculating the sample size for the planned Phase III trial.

Regarding safety, with regard to EM, no serious (or critical) adverse events have occurred in pPROM cases at Jichi Medical University, except for vascular pain, which has been treated with a protocol similar to that used in this study. In addition, antimicrobials are often administered for pPROM, usually for up to 2 weeks. In addition, there have been no reports of serious (or critical) adverse events of EM to mothers and infants at academic meetings to our knowledge. On the other hand, we believe that the incidence of adverse events and safety of the use of AZM should be investigated in detail because the dose and the number of days of administration of AZM are higher than those used in previous clinical trials. If a causal relationship is determined to be found, we have also established a system to ensure that the clinical research insurance will provide adequate compensation. If a large number of serious adverse events occur during the course of the study, we will consider cancellation of the entire trial.

In conclusion, ABPC/STB + AZM administration is expected to be more effective than ABPC/AMPC + EM administration recommended outside of Japan in preventing and treating intrauterine infection, and is expected to prevent the onset of BPD by preventing the transition to fetal lung injury and neonatal lung infection and inflammation via amniotic fluid inflammation and infection mainly by *Ureaplasma* spp.

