### 9.2 CAUSAL RELATIONSHIP WITH STUDY

CI or SI should determine the causal relationship between the trial and all adverse events that occurred in subjects (mother, fetus) and serious adverse events that occurred in infants. Judgment should be made not only due to the time relationship with the start of intervention treatment, but also due to complications, concomitant medications, study procedures, accidents, and other external factors. The causal relationship should be judged and recorded according to the following two criteria (A and B):

A “Causal or undeniable”: judgment is made according to the following a-c, whether known or unknown to occur during the clinical trial or interventional treatment:

- a: Reasonable or possible due to study or interventional treatment.
- b: There is a temporal relationship with the study.
- c: No other cause is shown, and a causal relationship with study cannot be denied.

B “No causal relationship”: judgment is based on the following d-f:

- d: It is not rational to have resulted from study or interventional treatment.
- e: No time relationship is shown.
- f: Other causes are shown.

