### 9.3 SEVERITY

CI or SI determines the severity of adverse events that occurred in subjects (mother, fetus) in the following three stages (A to C):

- A “mild”: It is transient, does not impair daily life, and does not require treatment.
- B “moderate”: It causes some problems in daily life and discomfort, and requires treatment.
- C “severe”: It markedly impairs daily life, and treatment such as hospitalization is required.

The CI or SI determines the severity of the adverse event in the child using the Neonatal INC version 1.0 Japanese translation.

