### 9.5 COLLECTION AND TRACKING PERIOD

CI or SI should collect and record adverse events starting from the treatment start date. Clinical findings present on the date of consent are considered complications and not adverse events. However, exacerbations of complications are recorded as adverse events. As a rule, “disease etc.” and serious adverse events that are determined to have a causal relationship with the trial should be followed up to recovery or improvement as much as possible. Follow-up should be terminated when CI determines that further recovery is difficult or unfollowable due to death, disability, sequelae, etc. Non-serious adverse events that are not causally related to the trial are not specifically followed up in the trial, regardless of the outcome.

Regardless of the severity of adverse events, any adverse events that occur should be collected and recorded until the end of each subject's participation in the trial.

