### **11.2 ANTICIPATED DISADVANTAGES**

Because subjects will be randomly assigned to either the study or control group, they will not be able to choose their preferred treatment. Regardless of which group they are assigned to, they may experience side effects (e.g., diarrhea) from the antimicrobial agents administered. Vascular pain may occur while receiving Erythrocine for Intravenous Infusion or ZITHROMAC Intravenous use.

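### Section 9.1.1 counts only undefined, clinically problematic events as adverse events, so open-label sites may under-record mild maternal and fetal events, possibly differently by arm

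*Protocol*

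**What the plan says.** Protocol 9.1.1 sets the threshold for the mother and fetus: "Adverse events in this study are defined as clinically problematic events among all unfavorable symptoms, signs, illnesses, and laboratory abnormalities". For infants it repeats the restriction: "In infants, they are defined as clinically problematic events among all unfavorable symptoms, signs, illnesses, or abnormal laboratory abnormalities". Neither place says what makes an event clinically problematic.

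Section 9.3 grades maternal and fetal events in three steps, the lowest described as: "It is transient, does not impair daily life, and does not require treatment". Section 9.5 states: "Regardless of the severity of adverse events, any adverse events that occur should be collected and recorded". It also says who does this: "CI or SI should collect and record adverse events starting from the treatment start date" (CI and SI are the chief and sub-investigators at the site).

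The trial is open-label (4.1). Blinded assessment covers only the BPD diagnosis (16.6), and there is no efficacy and safety committee (16.5). Comparing the safety of AZM and EM belongs to the primary objective (1.1, 3). Section 14.2.4 tabulates adverse events and side effects, with numbers, frequencies and 95% confidence intervals, for intervention against control.

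**The concern.** A clinical-relevance test on laboratory values is ordinary practice. A test on every symptom, sign and illness, with no stated criterion, is different: two sites can treat the same short episode of loose stools in opposite ways and both comply. The events most likely to be dropped are those that 9.3 would grade as mild.

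The judgment is made by people who know the arm, before anything reaches the adverse event form. Section 2.1.3 gives a possible reason to look harder in one arm. It reports local EM experience as free of serious or critical events apart from vascular pain, but says of AZM that "the incidence of adverse events and safety of the use of AZM should be investigated in detail", because dose and duration exceed those of earlier trials.

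At stake is the adverse event and side-effect comparison. An analysis plan cannot restore events that never reached the adverse event data, so the place to deal with this is the protocol's definition.

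**Working it through.** **Step 1: the passages side by side.**

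- 9.1.1: an unfavorable occurrence becomes an adverse event only if it is clinically problematic. No criterion.
- 9.3: an adverse event may be transient, leave daily life unimpaired and need no treatment. So some events of little consequence are expected to pass 9.1.1, but the text does not say which.
- 9.5: recording is independent of severity, but its object is adverse events, that is, what has already passed 9.1.1.
- 7.5.1 item 7 and 9.6: only adverse events go to the adverse event part of the eCRF.

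Nothing later in the chain captures, as an adverse event, what 9.1.1 removes.

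**Step 2: what is exposed.** Critical events are named one by one (9.1.2) and serious events have stated criteria (9.1.3). For infants only serious events are entered (9.6). Laboratory values and vital signs go into the eCRF in any case (7.5.2) and are summarised (14.2.4). That leaves non-serious maternal and fetal events, mainly mild ones.

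**Step 3: possible size.** The protocol gives no adverse event rate, so there is no figure of its own to reproduce. The only input from the documents is 50 women per arm (5.2.1). The rest are assumptions:

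- t, true proportion of women with an event, equal in both arms: 30% or 50%
- m, share of those whose event is mild: 50% or 70%
- a and e, share of mild events recorded with AZM and with EM: 80% v 60%, or 90% v 50%
- all non-mild events recorded in both arms

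Recorded proportion with AZM = t(1 − m) + t·m·a, and with EM = t(1 − m) + t·m·e. The false difference is t·m·(a − e). Its standard error (SE) is the square root of [pA(1 − pA) + pE(1 − pE)]/50, where pA and pE are the recorded proportions.

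| t | m | a v e | AZM | EM | False difference (points) | SE (points) |
|---|---|---|---|---|---|---|
| 30% | 50% | 80% v 60% | 27.0% | 24.0% | 3.0 | 8.7 |
| 30% | 70% | 80% v 60% | 25.8% | 21.6% | 4.2 | 8.5 |
| 50% | 50% | 80% v 60% | 45.0% | 40.0% | 5.0 | 9.9 |
| 50% | 70% | 80% v 60% | 43.0% | 36.0% | 7.0 | 9.7 |
| 30% | 50% | 90% v 50% | 28.5% | 22.5% | 6.0 | 8.7 |
| 30% | 70% | 90% v 50% | 27.9% | 19.5% | 8.4 | 8.5 |
| 50% | 50% | 90% v 50% | 47.5% | 37.5% | 10.0 | 9.8 |
| 50% | 70% | 90% v 50% | 46.5% | 32.5% | 14.0 | 9.7 |

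Example, last row: 0.5 × 0.3 + 0.5 × 0.7 × 0.9 = 0.465, and 0.5 × 0.3 + 0.5 × 0.7 × 0.5 = 0.325.

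The false difference runs from about 0.3 SE (3.0/8.7) to about 1.4 SE (14.0/9.7). Putting AZM higher is arbitrary; swapping the shares reverses the sign. With 70% of mild events recorded in both arms the difference is zero, but both rates are too low: for t = 50% and m = 70%, the table would show 0.15 + 0.35 × 0.7 = 39.5% in each arm.

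**The case against.** A reader might infer that 9.1.1 contradicts 9.3 and 9.5. It does not. A transient, untreated event can still be judged clinically problematic, and a mild grade together with recording at any severity suggests that mild events are meant to be captured. What stands is a tension that cannot be resolved consistently without a criterion.

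A reader might also infer that knowledge of the arm decides what is counted, or that AZM will look worse. The documents show neither. Section 11.2 says that women in either group "they may experience side effects (e.g., diarrhea) from the antimicrobial agents administered", and it names vascular pain for both infusions. Section 2.1.3 is background rationale, and it flags vascular pain for EM. The direction of any bias is open.

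Part of the exposure comes from the open label itself. Under any wording, unblinded staff still elicit symptoms and judge what is unfavorable. This stands: a wider definition reduces the room for judgment but does not remove it.

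Nor are the dropped events necessarily lost altogether. New symptoms are assessed on a fixed schedule (7.5.1 item 2), interruptions and withdrawals of study drug are entered with reasons (7.5.1 item 3), and medical records are source documents (16.1). But item 2, unlike the items that follow it, does not ask for eCRF entry, and 14.2.4 lists no analysis of it. A mild symptom in the chart still misses the safety table.

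Finally, section 9 refers details to a separate procedure that is not shown and may define the term. The protocol's own definition is still the one that restricts the count.

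**Conclusion.** The point holds in a limited form. The protocol restricts adverse events by an undefined judgment that reaches symptoms, signs and illnesses, and staff who know the arm apply it. Non-serious maternal and fetal events, mainly mild ones, may be under-recorded, and the arm may influence which are recorded.

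The size is illustrative only. It rests on assumed event rates, mild shares and recording shares, with only mild events filtered: about 3-7 points for a 20-point recording gap and 6-14 points for a 40-point gap. Most of these differences are at or below one standard error. The 14.2.4 comparison is descriptive, with no stated test, so the harm would be a misleading table and not a false claim of significance. It is worth changing because safety is part of the primary objective and the change is cheap.

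**What to change.** In 9.1.1, define a maternal or fetal adverse event as any unfavorable symptom, sign or illness arising after the start of protocol treatment, whatever its clinical importance or cause. Keep a clinical-relevance rule for laboratory values only, and state it. Sections 9.3 and 9.5 then work as written.

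Record diarrhea and vascular pain, which 11.2 anticipates in both arms, by the same yes/no question in both arms at the adverse event checks already in the schedule. No visit, treatment or clinical rule changes.

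The cost is the wording, two eCRF questions, and more mild events to enter and code. Timing matters too. This edition is dated November 29, 2023, and registration is planned from April 1, 2022 to March 31, 2024, so about 20 of 24 months have passed. If the change is adopted mid-trial, the safety tables must identify events recorded before and after it, so that two definitions are not pooled unseen.

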f. CI or SI must obtain consent before starting examination during the screening period.

g. CI or SI should care for patients in hospital at least for the period from the start of protocol treatment to 3 days after delivery.

- h. CI or SI must start protocol treatment within 4 days after obtaining consent.
- i. CI or SI should examine the estimated fetal weight once a week at or after Week 3, until the decision to terminate the pregnancy. However, the hematological examination and blood biochemical test should be performed only when needed at or after Week 4, until the decision to terminate the pregnancy.
- j. CI or SI should not take biological specimens from patients if the patients become complicated with COVID-19 infection. In addition, all preserved specimens should be abandoned.
- k. If CI or SI decides to cancel participation in the trial due to the adverse events, CI or SI should continue the investigation of adverse events due to the test drugs or drugs used concomitantly which are the reasons for the cancelation of participation in the trial, from the cancelation to the one-month postpartum medical examination.
- l. CI or SI should investigate the occurrence of adverse events in the subject (mother and fetus). As for the mother, CI or SI should investigate from the starting day of protocol treatment to the observation period after the termination of pregnancy (or day of cancelation of participation in the trial). As for the fetus, CI or SI should investigate from the starting day of protocol treatment to the termination of pregnancy (or day of cancelation of participation in the trial). However, if CI or SI decides to cancel participation in the trial due to the appearance of adverse events, CI or SI should continue the investigation of adverse events due to the test drugs or drugs used concomitantly which are the reasons for the cancelation of participation in the trial, from the cancelation to the one-month postpartum medical examination.
- m. CI or SI should investigate the decision day of the termination of pregnancy, the time (day, hour, minute) of delivery, the reasons for termination of the pregnancy (both maternal and fetal causes).
- n. CI or SI should investigate the delivery mode, presence/absence of stillbirth and the day of stillbirth, placental weight, and presence/absence of placental infarction.

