#### (3) Status of study drug administration

Enter the following items into the eCRF

- Date and number of times the study drug is administered

- Daily dose of study drug
- Whether there has been an interruption, and if so, the reason for the interruption
- Whether or not medication has been withdrawn, and if so, the reason for such withdrawal

Time of implementation: Treatment observation period

(4) Survey on termination of pregnancy

The date of decision of the termination of pregnancy, the reason for the decision of the termination of pregnancy (maternal and fetal requirements), the date of the termination of pregnancy, and the time the fetus was delivered are investigated and the results are entered into the eCRF.

Time of implementation: At the end of pregnancy

(5) Delivery findings

The mode of delivery (spontaneous delivery, induced delivery, cesarean section, vacuum delivery, or breech extraction) and, in the case of cesarean section, the presence or absence of maternal indication and its description, presence or absence of fetal indication and its description, stillbirth and the date of confirmed death, placental weight, and placental infarction are investigated and the results are entered in the eCRF.

Time of implementation: At the end of pregnancy

(6) Check concomitant medications

Check concomitant medications and enter the results into the eCRF. Uterine contraction suppressants (type also asked), antihypertensive drugs, insulin, psychotropic drugs, antiepileptic drugs, salazopyrine, thyroid drugs, thiamazole/propylthiouracil, antitumor drugs, inhaled steroids, bronchodilators, low-dose aspirin and heparin self-injection are only investigated during screening phase and the results are entered into the eCRF.

Time of implementation: screening period, treatment observation period, observation period after termination of pregnancy, at cancelation of participation in the trial, and follow-up after cancelation of participation in the trial.

(7) Confirmation of adverse events

Adverse events should be identified and the results are entered into the eCRF.

Time of implementation: Treatment observation period, observation period after termination of pregnancy, at cancelation of participation in the trial, and follow-up after cancelation of participation in the trial.

---

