#### 9.1.2 DEFINITION OF CRITICAL ADVERSE EVENTS

Critical adverse events in this trial are IUFD, sepsis, ICU admission, multiple organ failure, artificial ventilation, and total hysterectomy in subjects (mother, fetus).

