### 9.6.2 REPORTING OF “DISEASE, ETC.”

If a serious “disease, etc.” (a serious adverse event for which a causal relationship cannot be ruled out) occurs, the SI who has knowledge of the event will report it to the CI at his/her institution. Upon receiving the report, the CI will report it to the administrator of the medical institution at that institution and notify the PI and the study office. Thereafter, depending on the predictive nature of the “disease, etc.”, PI must report to the Jichi Medical University Central Clinical Research Ethics Committee and the Minister of Health, Labour and Welfare by the reporting deadline.

Submission deadline for unapproved/off-label use

|   | Type of adverse events                                                                                                                                                                                                 | Causal relationship | Predictive nature | Deadline for Central Clinical Research Ethics Committee | Deadline for Minister of Health, Labour and Welfare |
|---|------------------------------------------------------------------------------------------------------------------------------------------------------------------------------------------------------------------------|---------------------|-------------------|---------------------------------------------------------|-----------------------------------------------------|
| 1 | 1 Death or risk of death                                                                                                                                                                                               | Present             | Possible          | 7 days                                                  | 7 days                                              |
|   |                                                                                                                                                                                                                        |                     | Not possible      | 15 days                                                 | -                                                   |

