## 10.2 CANCELATION OF THE ENTIRE TRIAL

If the following situations (1. to 6.) occur and the investigator (CI or PI), Jichi Medical University Central Clinical Research Ethics Committee, or director of the implementing medical institution decides that the entire trial should be discontinued, the entire trial may be canceled. This situation is called “cancellation of the entire trial”.

1. When an unpredictable serious “disease etc.” occurs and there is concern about disadvantage to the subject (mother, fetus, infant).
2. When a critical violation/non-compliance with the law and related laws or study plan is found.
3. When a fact that impairs or may impair ethical validity or scientific rationality is obtained.
4. When a critical risk to the subject is identified.
5. When an opinion is given by the Jichi Medical University Central Clinical Research Ethics Committee.
6. When the Minister of Health, Labour and Welfare requests cancellation or makes a recommendation.

In the event of cancellation in the entire trial, the PI will report to the CIs of all the implementing medical institutes, Certified Clinical Research Review Board, and to the administrators of the implementing medical institutions. In addition, the PI will contact the subjects and inform them of the change in the study schedule. In the event of cancellation of the entire trial, the subject will promptly discontinue the protocol treatment, and the safety of the subject (mother and fetus) will be ensured in accordance with the discontinuation criteria in 6.2.6 Criteria for discontinuation of protocol treatment.

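### Section 9.1.1 ends the maternal adverse-event window at delivery while three other rules run past it, and the 9.6.2 table as printed gives unpredictable related serious events the weaker expedited report

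*Protocol*

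**What the plan says.** **Maternal window.** Section 9.1.1 applies one window to mother and fetus together: "from the start of protocol treatment to the termination of pregnancy", or until participation is discontinued. Note l of Table 1.3-1, repeated under Table 7.5-1, separates the two. The fetus is followed to the end of the pregnancy, but the mother is followed "from the starting day of protocol treatment to the observation period after the termination of pregnancy". Section 7.5.1(7), on confirming adverse events, agrees: "Time of implementation: Treatment observation period, observation period after termination of pregnancy, at cancelation of participation in the trial", and it adds follow-up after cancellation. Section 9.5 says that "any adverse events that occur should be collected and recorded until the end of each" subject's participation.

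Section 9.1.2 lists six critical adverse events: intrauterine fetal death, sepsis, ICU admission, and then "multiple organ failure, artificial ventilation, and total hysterectomy in subjects (mother, fetus"). It gives no time limit.

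**Expedited reporting.** Section 9.4 judges predictability against the package insert and interview form, and calls an event that does not match them unknown. Section 9.6.2 makes the deadline for related serious events depend on predictability, in a table headed "Submission deadline for unapproved/off-label use" with rows labelled 'Possible' and 'Not possible'. Section 10.2, item 1, gives as a ground for cancelling the whole trial that an unpredictable serious 'disease, etc.' "occurs and there is concern about disadvantage to the subject".

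**The concern.** Critical adverse events are a declared safety outcome. Section 2.1.3 says that the AZM dose and number of treatment days exceed those of earlier trials, so safety needs detailed study. The trial has no efficacy and safety committee (16.5) and no interim analysis (14.2.6). It therefore leans on consistent event classification and on prompt case reports.

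If two sections give different ends to the maternal window, two sites can classify the same postpartum event differently, in an open-label trial. If the reporting table favours events that were already foreseeable, the ethics committee, which is one of the bodies that may cancel the trial, hears late or only in the annual report about the kind of event that 10.2 names first.

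**Working it through.** No figure in the plan needs recalculating. The check sets the rules side by side.

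**Step 1: where the maternal window ends.**

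| Source | End of the window for the mother |
|---|---|
| 9.1.1 (definition) | termination of pregnancy |
| Note l, Tables 1.3-1 and 7.5-1 | into the observation period after delivery |
| 7.5.1(7) | includes the observation period after delivery |
| 9.5 | end of the subject's participation |

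One definition stands against three collection rules. The adverse-event row of both schedule tables is also marked at delivery and at the maternal discharge examination.

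**Step 2: does the definition matter if the data are collected anyway?** It does, because later rules are built on it. Section 9.1.3 makes a serious adverse event an adverse event that meets a seriousness criterion. Section 9.1.4 draws 'disease, etc.' from adverse events. Section 9.6 ties eCRF entry and reporting to adverse events, and 14.2.4 tabulates adverse, serious and critical events. If 9.1.1 governs, maternal sepsis on the day after delivery is not an adverse event, and so is neither a serious adverse event nor reportable 'disease, etc.'. If note l and 9.5 govern, it can be all three.

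**Step 3: which critical events are affected.** Of the six in 9.1.2, only intrauterine fetal death must precede delivery. The other five (6 − 1 = 5) can occur at or after it. Note g keeps mothers in hospital for at least 3 days after delivery, so the disputed interval is not trivial.

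**Step 4: the collection rules do not share one end either.** The schedule's last routine maternal visit is the discharge examination, whereas 4.1 runs the post-termination phase to the child's discharge. Following note l therefore still leaves the end point open.

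**Step 5: the 9.6.2 table, causally related events.**

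| Class | Predictability | Committee | Minister |
|---|---|---|---|
| Death or risk of death | Possible | 7 days | 7 days |
| Death or risk of death | Not possible | 15 days | none |
| Other serious (classes 2 to 5) | Possible | 15 days | 15 days |
| Other serious (classes 2 to 5) | Not possible | none | none |

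Deadlines are set in 4 of 4 cells for 'Possible' and in 1 of 4 for 'Not possible', and that one is 15 − 7 = 8 days later than its counterpart. Read with 9.4, 'Not possible' is the unknown event. The table therefore runs against 10.2, item 1.

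**Step 6: cross-reference.** A footnote in 17.1 limits reports to the Minister to the scope of a section 9.5.3. Section 9.5 has no subsections; the reporting rule is in 9.6.2.

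**The case against.** The strongest reply is that these are wording faults, not lost data, and much of it stands.

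- A reader might infer that postpartum events drop out and that the hysterectomy count is close to zero by construction. The documents do not support this. Three rules schedule collection after delivery, 9.1.2 is a free-standing list with no time cut, and 14.2.4 tabulates critical events without a cut at delivery. What remains is that the status of these events is contradictory, above all as adverse or serious events.
- A reader might infer from the table that unpredictable related events are reported to nobody. That is wrong. Under 9.6.1 every serious adverse event goes promptly to the principal investigator and secretariat, and on to the other sites. Under 9.6.2 related ones also go to the institution's administrator. All 'disease, etc.' enter the annual report to the committee. Only the expedited committee and Minister deadline is weaker or absent, and the upper row covers risk of death as well as death.
- Expedited reports are not the only route to stopping. Section 10.2 also lets the investigator or the institution's director decide, and they receive these events directly.
- The labels may be a translation slip, and section 9 defers details to a separate 'disease, etc.' procedure that is not shown. This is fair. It is a reason to check that procedure before swapping rows, not a reason to leave the table as it is.

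**Conclusion.** Both parts hold as internal contradictions that should be corrected. Neither shows that events will be missed.

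(1) The definition in 9.1.1 conflicts with three collection rules, so whether postpartum cases of five of the six critical events are adverse or serious events, and how they enter the 14.2.4 tables, depends on which section a site follows. The number of events affected cannot be given, because the protocol states no expected postpartum rates.

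(2) Read literally, unpredictable related serious events get 15 days to the committee and no Minister report (death or risk of death), or no expedited deadline to either body (other serious events). This conflicts with 10.2, item 1. It rests on the English labels meaning what they say and on 9.4 defining predictability. If the rows are interchanged by mistake, the fault is in the labels alone, but a site working from this text would still be misdirected.

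**What to change.** - Amend 9.1.1 to separate mother from fetus, as note l does, so that the maternal window extends through the observation period after delivery.
- State one end point for the mother, choosing explicitly between the discharge examination (last routine maternal visit in the schedule) and the child's discharge (4.1). Align 9.5 and note l with that choice, and leave the existing rule on follow-up after cancellation as it is.
- State that this window applies to the serious and critical event tables in 14.2.4.
- Reconcile the predictability rows in 9.6.2 with 9.4, 10.2 and the separate 'disease, etc.' procedure, and relabel them known and unknown. If the rows prove to be interchanged, correct them so that unpredictable related serious events do not get the slower or absent expedited report.
- Correct the reference to section 9.5.3 in 17.1.

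The cost is a protocol amendment of a few lines and a notice to sites. If the discharge examination is chosen, no new visit or data item is needed, because Table 1.3-1 already marks adverse-event confirmation there. If the child's discharge is chosen, the schedule must say how maternal events are ascertained after the mother goes home.
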